**Blinding of participants**

The trial will be presented as study to evaluate the effectiveness of magnetic and copper bracelets on arthritis symptoms. All communication will simply state that one or more of the devices being tested might be intended to act as a placebo.

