**Blinding of health care staff**

GPs, practice nurses and phlebotomists will be provided with similar information about the trial to that given to patients. At no point will they be informed which of the four devices are intended to act as placebos. This will help to maintain blinding amongst participants. Members of staff from participating practices who take part in focus groups before the trial begins will be provided with additional information about the devices involved. These individuals will be asked to refrain from discussing this information with colleagues or patients.

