**Exclusion criteria**

- Pregnancy
- Pacemaker or similar device
- Not responsible for administering his/her own medication.
- Dementia or memory impairment, either documented in medical records or if suspected indicated by a score of 6 or below on the Abbreviated Mental Test (Wong et al 2004).
- Diagnosis of malignant disease within medical records
- Forthcoming orthopaedic surgery or analgesic injections within the next 25 weeks.
- Known allergy to copper.
- Regular use of a magnetic or copper bracelet at recruitment
  1. **What is the proposed duration of treatment period?**

Participants begin the first treatment phase immediately after recruitment. Participants will undergo four treatment phases, each lasting five weeks. Each treatment phase will be separated by a one week ‘wash out’ period. Total duration for participation therefore will be 23 weeks.

- 1. **What is the proposed frequency and duration of follow up?**

Baseline questionnaire data will be collected at recruitment. Participants will then be followed up on four further occasions, separated by intervals of six weeks. These will occur at the end of each treatment phase. Blood samples should be taken within a two day period either side of each planned follow-up.

- 1. **What are the proposed outcome measures?**

The recommended approach for assessment of outcomes in clinical trials of treatments for RA is to examine change according to a ‘core set’ of disease activity measures defined by the American College of Rheumatology (ACR). This consists of seven measures. Three of these are self report measures; pain, physical function and global assessment of disease activity. Three rely on clinical examination; swollen joint count, tender joint count and professional assessment of disease activity. With the final measure involving serum analysis of acute phase reactants. (Arnett et al 1988, Felson et al 1993, Felson et al 1995, Rindfleisch and Muller 2005).

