Quality of life, medication use and data relating to health care expenditure will be collected as part of the trial. If magnet therapy is shown to be effective for reducing either arthritis symptoms or medication use then a cost-effectiveness analysis will be conducted. This will be lead by staff from the Centre for Health Economics at The University of York.

- 1. **What is the estimated research cost for the trial?**

Total: £13,635 excluding salaries. This is based on: £6900 in order to reimburse general practices (see below); £2000 for research travel expenses; £1800 for device costs; £1035 for trial participant expenses; £1000 printing and administration; £500 focus group expenses; £400 telephone charges.

- 1. **What will be the NHS cost implications for the trial?**

The trial will reimburse general practices for costs incurred in supporting this trial. This relates to time of nurses, phlebotomists, clerical staff and GPs in performing research activities which place a strain on resources. Activities include identifying / contacting patients as part of recruitment. Clerical staff will also book and accommodate participant appointments. Blood samples will be taken from each participant on a maximum of four occasions. In each case this will involve two samples. In total, general practices will be reimbursed up to £100 per participant. Payments will be issued on the basis of £25 per visit. This assumes haematology charges of £10.15 for CRP, £6 for PV and £8.50 for staff time. This amounts to a maximum of £6900, although the actual figure is likely to be lower as some participants will fail to provide a complete set of blood samples.

- 1. **Over what period is funding requested?**

N/A

- 1. **Is a pilot feasibility stage planned?**

A pilot study has already been conducted in order to test several methodological features of the proposed trial, i.e. MACROPOD.

Before patient recruitment begins, two focus groups will be formed.One involving GPs, practice nurses and phlebotomists. Members of this group will be drawn from practices which express an interest in participating in CAMBRA. The other will consist of people with RA and those involved in providing direct support to people with RA. These will be drawn from members of community support groups for people with affected by RA and not via NHS channels.

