Each focus group will be provided with a detailed outline for the proposed trial, together with trial materials in advance. Feedback will be sought on a variety of issues, including possible weaknesses with trial methodology and suitability of written material. The groups will help to identify any special considerations associated with the study of rheumatoid arthritis which may have been overlooked. Each group will also discuss issues specific to the use of blood tests, such as their acceptability to study volunteers. Information gathered will be used to refine the trial protocol. This may result in an application for the approval of minor amendments from local research ethics committee concerned.

1. **DETAILS OF THE TRIAL TEAM**
   1. **Trial management**

The Department of Health Sciences at The University of York will act as the co-ordinating centre for CAMBRA. This trial will be led by [name] as the chief investigator, who will be responsible for clinical and scientific co-ordination, together with day to day management. This will include recruitment of all general practices and participants, data collection, analysis and dissemination of findings. [name], as Director of the York Trials Unit will be responsible for supervising patient randomisation and data management. He will also act as an advisor on matters relating to trial design and methodology. [name] will act advisor on matters concerning the use and evaluation of complementary and alternative medicine. [name] will serve as a statistical advisor to the trial. [name] from The University of Hull will advise on matter concerning general medical practice. As a co-investigator for MACROPOD, he will also contribute towards the evaluation of this trial. For the purpose of trial development further support will be sought from a leading rheumatologist.

- 1. **Participating centres**

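### People with RA on the pre-trial focus group probably learn which devices are controls, yet they are neither excluded from enrolling nor asked to keep this to themselves

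*Protocol*

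**What the plan says.** Under the heading on a pilot feasibility stage, the protocol plans two groups: "Before patient recruitment begins, two focus groups will be formed". One is made up of practice staff. "The other will consist of people with RA and those involved in providing direct support to people with RA". On the source of this second group: "These will be drawn from members of community support groups for people with affected by RA and not via NHS channels".

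Both groups receive the same kind of material: "Each focus group will be provided with a detailed outline for the proposed trial, together with trial materials in advance". They are asked to appraise the design: "Feedback will be sought on a variety of issues, including possible weaknesses with trial methodology and suitability of written material".

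Participant blinding rests on limited disclosure. Under Blinding of participants: "All communication will simply state that one or more of the devices being tested might be intended to act as a placebo".

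Blinding of health care staff says that practice staff who attend a focus group receive extra information about the devices, and then: "These individuals will be asked to refrain from discussing this information with colleagues or patients". No matching request is made of the RA and supporter group.

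The exclusion list has eight items, the last being "Regular use of a magnetic or copper bracelet at recruitment". None concerns focus-group membership or prior knowledge of the design.

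**The concern.** The protocol sees that focus-group knowledge could leak and guards one route, staff telling patients. It leaves open the more direct route: a person with the trial disease who has read the outline and then enrols, or who tells fellow support-group members who enrol.

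This matters more here than in most placebo-controlled trials. The background section accepts that magnetism can usually be detected without difficulty. Concealing the sequence therefore does not fully protect blinding, and two of the three controls depend on participants not knowing what they are for. The attenuated strap works as a control if it is not recognised as one. The copper bracelet works if the wearer expects some benefit from it. A person who knows that a weakened strap is in the set can compare the pull of the straps, and a person who knows that copper is there as a comparator may lose that expectation.

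The primary outcome is a self-reported pain VAS. In a four-period crossover, each informed completer contributes to every device contrast.

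**Working it through.** The protocol gives no figure on this point, so the main check sets the sections side by side.

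1. *Do people with RA see the outline?* Yes. The pilot-stage section gives it to each group, without distinction.
2. *Does the outline reveal the roles of the devices?* Not stated. It is inferred from the outline being detailed and from the request to comment on weaknesses in the methodology, which is hard to do without knowing the controls. Extra device information is stated explicitly only for practice staff.
3. *Are members asked to keep it confidential?* Only the staff are.
4. *Do the eligibility rules keep members out?* No. None of the eight exclusions applies, and the inclusion criteria do not touch on it.
5. *Does the recruitment route keep them out?* Not by rule. Participating centres describes identifying patients from practice records and inviting them by post, with no step that screens out focus-group members. Drawing the group from outside the NHS governs how the group is formed, not who may later be invited.
6. *Would a member know the allocation?* No. Sequences are generated remotely and concealed, and devices come in sealed boxes.

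**Context from the sample size section.** The assumed means are 65 for demagnetised, 52 for full strength (65 − 13) and 58.5 for each of the other two (65 − 6.5), with SD 21.7 mm. These give f = 0.2118. A one-way analysis of variance with 62 per device then has power 0.802, and 62 is the smallest number reaching 80%. Allowing for attrition, 62 / 0.90 = 68.9, so 69. Both stated figures reproduce, and the point does not depend on them.

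**Purely illustrative size.** The group size and its overlap with participating practices are not given. Assume 0 to 5 informed people among the 62 completers, and assume that knowledge alone produces a 13 mm difference in each of them. The 13 mm borrows the protocol's whole assumed gap between full strength and demagnetised, so it is generous.

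- Share of completers: 0/62 to 5/62 = 0% to 8.1%.
- Shift in a device contrast: 0 to (5/62) × 13 = 0 to 1.05 mm.
- Standard error of a difference between two devices, taking 21.7 mm as the within-subject SD: 21.7 × √(2/62) = 3.9 mm.
- Ceiling relative to that standard error: 1.05 / 3.9 = 0.27.
- Ceiling relative to the assumed 6.5 mm between full strength and the attenuated or copper device: 1.05 / 6.5 = 16%.

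Neither the count nor the 13 mm has a source in the protocol, and the range includes zero.

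**The case against.** The strongest reply is that the crucial step is not written down. The contents of the outline are not listed, only staff are said to receive extra device information, and the rule on communication with participants could be read as covering the RA group too. That group may have been given a version that did not disclose the roles of the devices. This stands as a caveat: disclosure is probable, not established.

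Second, overlap is limited. The group comes from community support groups, whereas participants come from the lists of nine to twelve practices. A member would have to be registered at one of these, be identified, respond, meet the pain and analgesic criteria, and consent. This lowers the probability without removing it, and no overlap is shown. Onward briefing within a support group is possible but speculative.

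Third, part of the information is not secret. The trial is presented to everyone as a study of magnetic and copper bracelets, example devices are shown at the recruitment meeting, and the protocol itself expects the demagnetised strap to be recognised. The added exposure is therefore mainly the existence of the attenuated strap and the role of copper. That is a fair narrowing, but those are the two controls that depend most on not being recognised.

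Fourth, participants will be asked whether they judged each device to be a placebo. As described, this records a guess rather than prior knowledge of the design, and it measures a failure of blinding without preventing it.

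Finally, instructions to focus-group members may sit in their invitation material, which is not at hand. That could answer the confidentiality part. It would not change the eligibility rules, which as written admit these people.

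**Conclusion.** The point holds as a minor gap with a cheap remedy. The protocol limits what participants may be told, gives what is probably fuller information to a group with the same disease, and places no barrier between that group and enrolment.

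A reader might infer that unblinded participants will be randomised. The documents do not support that: sequences stay concealed, the outline's contents are not stated, and no focus-group member is shown to be registered at a participating practice. What can be said is that someone probably aware of the control devices could enrol and could recognise them more easily.

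The size cannot be derived. It is probably small and may be zero. The ceiling of about 1 mm, or 0.27 of a standard error, rests on two unsupported assumptions (up to five informed completers and a 13 mm effect in each) and should not be quoted as an estimate of bias. The direction is not fixed either, since it depends on what the informed person expects of each device.

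**What to change.** - Add to the exclusion criteria: *took part in a CAMBRA focus group or has seen the detailed trial outline*.
- Ask one question on this at the recruitment meeting, where eligibility is already assessed.
- Extend the request under Blinding of health care staff to the RA and supporter focus group, asking them not to discuss the devices with anyone who might take part.

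The cost is one line, one question and one sentence, plus at most a handful of candidates out of the 216 approached. The planned recruitment leaves little slack (108 assessed − 38 lost = 70, against 69 needed), so even a few exclusions could mean inviting a few more patients. The protocol already allows for up to three further practices if too few patients are identified, and it anticipates minor amendments after the focus groups.
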